### Study population

The study population consists of 140 women undergoing pelvic lymphadenectomy for cervical and endometrial cancer in one of the three study sites, ie the Departments of Obstetrics and Gynecology at the Ruhr University Bochum, the Gynecologic Oncology Center at the Charles University in Prague, and the Medical University of Vienna fulfilling the inclusion/exclusion criteria requirements.

### Outcome variables

2.8.1. The incidence of symptomatic pelvic lymphoceles CTCAE 4.03 grade ≥2 within 4 weeks after surgery in women undergoing open or laparoscopic pelvic lymphadenectomy for cervical or endometrial cancer (primary outcome variable).

2.8.2. The incidence of sonographically detected pelvic lymphoceles of at least 2 cm in the largest diameter 4 weeks after surgery in women undergoing open or laparoscopic pelvic lymphadenectomy for cervical and endometrial cancer with and without the application of Tachosil® during surgery (secondary outcome variable).

2.8.3. The rate and type of medical interventions for clinically symptomatic pelvic lymphoceles such as analgesics and/or lymphocele puncture and drainage (secondary outcome variable).

2.8.4. The length of hospital stay (secondary outcome variable).

2.8.5. The rate of predefined complications, ie abscess in the pelvis, fever >38°C on at least two occasions >24 hrs apart, leg swelling, local pelvic bleeding complications necessitating a surgical intervention (secondary outcome variable).

### Statistical analysis

A power calculation demonstrated that, with a sample size of 70 per group, a two-arm study has a power of 80% to detect a 66% absolute difference in treatment efficacy at a significance level of 0.05 regarding the primary outcome parameter, ie symptomatic lymphoceles CTCAE 4.03 grade ≥2. This calculation was based on published data by Tinelli et al. observing a rate of 32% of symptomatic lymphoceles in the placebo group and 10% in the Tachosil® group [5]. Assuming a 10% drop out-rate, 140 women will be randomized. The chi-square test will used for comparisons of frequencies and cross-tabulations. One Way ANOVA on ranks will be used on means. Descriptive statistics (means, standard deviations, and ranges) will be used for demographic data. Bonferroni’s correction will be used for multiple comparisons of secondary outcomes.

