**Methods/Design:**

We will perform a multicentre, blinded, randomized, controlled trial comprising 140 women with gynecologic malignancies undergoing pelvic lymphadenectomy. Women will be randomly allocated to Tachosil® application or no application. Primary outcome is efficacy, defined as lymphocele CTCAE 4.03 grade ≥2 within four weeks after surgery. Secondary outcomes are asymptomatic lymphocele verified by ultrasound, medical or surgical intervention. Assuming a two-sided 5% significance level, a power of 80%, and a drop out rate of 10%, a sample size of 68 patients per group was calculated to detect a 66% absolute decrease in symptomatic lymphoceles.

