### Study hypothesis

We hypothesize that the intraoperative application of two collagen-fibrin patches (Tachosil®) to the obturator fossa and the femoral canal will reduce the number of symptomatic pelvic lymphoceles by at least 66% (primary study end point).

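### The power statement and the abstract give the target effect as 66% absolute, but the planning rates of 32% and 10% differ by 22 percentage points (about 69% relative)

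*Protocol article*

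**What the plan says.** The target effect appears in three forms in the protocol article.

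- **Absolute, 66%.** The Statistical analysis section claims 80% power "to detect a 66% absolute difference in treatment efficacy at a significance level of 0.05". The Methods/Design paragraph of the abstract says "a sample size of 68 patients per group was calculated to detect a 66% absolute decrease in symptomatic lymphoceles".
- **As two event rates.** The sentence after the power statement bases the calculation on an earlier randomized trial in women, "observing a rate of 32% of symptomatic lymphoceles in the placebo group and 10% in the Tachosil® group".
- **A reduction of at least 66%, with no scale given.** The Study hypothesis section says that the patches "will reduce the number of symptomatic pelvic lymphoceles by at least 66% (primary study end point"). The end of the Background and the end of the Discussion repeat this figure.

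The other design inputs are a two-sided 5% level, 80% power and 10% dropout (abstract), and 70 women per group, 140 randomized (Statistical analysis). The only test named for frequencies is the chi-square test. The article gives no margin and no null hypothesis other than equality.

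**The concern.** The first two forms contradict each other in adjacent sentences. The word absolute is explicit in both the abstract and the power statement, so neither can be read as a relative reduction without changing the text.

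Readers use the target effect to judge whether the trial is large enough and what a result would mean. A reader of the abstract alone sees no event rates and cannot recover the true target. That reader would conclude that the trial was sized for an effect three times as large as the one actually assumed.

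The lesser concern is the third form. If a reduction of at least 66% is taken as the primary hypothesis, a significant chi-square result might later be reported as confirming it, which that test cannot do.

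**Working it through.** **1. Effect implied by the planning rates** (32% and 10%, Statistical analysis section)

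- Absolute difference: 0.32 − 0.10 = 0.22, or 22 percentage points.
- Relative reduction: 0.22 / 0.32 = 68.75%, about 69%.
- Largest possible absolute fall from 32%: 32 points. A fall of 66 points cannot occur.
- Reading efficacy as being free of symptomatic lymphocele: 90% − 68% = 22 points again.
- Ratio of stated to actual target: 66 / 22 = 3.

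**2. Reproducing the sample size** (two-sided 5%, 80% power, equal arms)

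n = [1.960 × √(2p̄(1−p̄)) + 0.842 × √(p₁(1−p₁) + p₂(1−p₂))]² / (p₁−p₂)², with p̄ = 0.21.

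- First term: 1.960 × √(2 × 0.21 × 0.79) = 1.129.
- Second term: 0.842 × √(0.2176 + 0.0900) = 0.467.
- n = (1.129 + 0.467)² / 0.0484 = 52.6, so 53 per arm without continuity correction.
- With continuity correction: n/4 × [1 + √(1 + 4/(n × 0.22))]² = 61.4, so 62 per arm.
- Dropout of 10%: 62 / 0.9 = 68.9, so 69 per arm. Adding 10% to 61.4 instead gives 67.5, so 68.

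This agrees with the stated 68 and 70 to within two women per arm. Without continuity correction the dropout-adjusted figure is 59, which does not. If 70 were the number before dropout, power would be about 90% uncorrected or 86% corrected, so 70 fits 80% power only as the number after dropout.

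**3. Other readings of 66%**

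| Reading | Rates | Evaluable per arm: uncorrected / corrected |
|---|---|---|
| 66 points absolute (assumed example) | 76% vs 10% | 8 / 11 |
| 66 points absolute (assumed example) | 98% vs 32% | 7 / 10 |
| Exactly 66% relative | 32% vs 10.9% (0.32 × 0.34) | 59 / 68 |
| Stated planning rates | 32% vs 10% | 53 / 62 |

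A true 66-point target would need about a tenth to a sixth of the planned size. The corrected 68 for exactly 66% relative equals the abstract's figure. However, the abstract lists dropout among its assumptions, and adding it takes 68 to 76. The Statistical analysis section also names 32% and 10% as the basis.

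**4. What a significant chi-square result shows**

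Take 63 evaluable per arm (70 × 0.9) and 20 events in the control arm (31.7%, close to 32%). With equal arms, X² = 126 × (a−b)² / [(a+b)(126−a−b)]. The corrected version replaces |a−b| by |a−b| − 1.

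- 20 vs 9: uncorrected 126 × 121 / (29 × 97) = 5.42, p=0.020. Corrected 126 × 100 / (29 × 97) = 4.48, p=0.034. The observed reduction is 1 − 9/20 = 55%.
- For 20 vs 9 the risk ratio is 0.45. The standard error of its logarithm is √(1/20 + 1/9 − 2/63) = 0.360, so the 95% interval is about 0.22 to 0.91.
- 20 vs 10, a 50% reduction: uncorrected p=0.036, corrected p=0.060. This case depends on the version of the test, which the article does not name, so nothing is rested on it.

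A reduction of at least 66% corresponds to a risk ratio of 0.34 or less. The interval for 20 vs 9 extends well above that, although the test is significant.

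**The case against.** The strongest reply is that this is one wrong word. The correct rates stand in the next sentence, so a reader of the methods can recover the target at once. The hypothesis passages do not say absolute and, with a control rate of about 32%, can only mean a relative reduction. The sample size was evidently computed from 32% versus 10%. All of this stands, and it limits the consequence. It does not remove the contradiction, and it does not help in the abstract, where no rates are given.

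Three stronger readings are tempting and not supported.

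- **That the trial is wrongly sized.** A reader might infer from the 66-point target that the sample size is invalid. Step 2 shows that it follows from the stated rates. The gap between 68 and 70 per group is a separate, small inconsistency.
- **That the trial plans to claim a reduction of at least 66% from a significant test.** The article sets no margin or success rule at 66%. Its primary aim is simply to evaluate incidence with and without the patch, which a test of equality fits. The figure reads most naturally as an expected effect, so the mismatch with the test calls for clarification and is not an error of design.
- **That 66% versus 68.75% is itself an error.** A planned reduction of 68.75% is compatible with at least 66%, and the lower figure may be loose rounding to two thirds.

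The absence of a stated effect measure and interval is not a finding either. Those details are commonly left to the full protocol or the analysis plan, which are not shown.

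**Conclusion.** The target effect is wrong as written in the power statement and in the abstract. It reads 66% absolute where the stated planning rates give 22 percentage points absolute, or about 69% relative. This rests only on the two rates in the Statistical analysis section and on subtraction.

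The error lies in the description of the effect and not in the design. Under a two-sided 5% level, 80% power, continuity correction and 10% dropout, 32% versus 10% gives 62 evaluable and about 69 randomized per arm, in line with the planned 140. The continuity correction is inferred from the fit, since the article does not state it.

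Secondarily, the hypothesis of at least 66% needs a scale and should be separated from what the test assesses. A significant result would show that the arms differ, not that the reduction reaches 66%.

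**What to change.** - In the Methods/Design paragraph of the abstract and in the Statistical analysis section, replace the 66% absolute decrease or difference with a 22 percentage-point absolute difference (32% versus 10%; about 69% relative reduction).
- In the Background, Study hypothesis and Discussion sections, mark the figure of at least 66% as a relative reduction and a planning expectation. Word the primary hypothesis as a difference between the arms in the proportion with symptomatic lymphocele.

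The cost is wording only. The number of patients, the primary outcome and the planned test stay as they are.

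### The Statistical analysis section uses 70 per group both as the number giving 80% power and as the number randomised after the dropout allowance, and the abstract's 68 is not reconciled with it; the enrolment of 140 is adequate

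*Protocol article*

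**What the plan says.** The Statistical analysis section of the protocol article reads: "with a sample size of 70 per group, a two-arm study has a power of 80" (per cent), the effect being described as an absolute difference of 66%. It takes the underlying rates from a published single-centre trial "observing a rate of 32% of symptomatic lymphoceles in the placebo group and 10% in the Tachosil® group", and then adds: "Assuming a 10% drop out-rate, 140 women will be randomized". The chi-square test is named for comparing frequencies. No continuity correction, formula or software is named.

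The Methods/Design paragraph of the abstract gives a different group size. There, with "a drop out rate of 10%, a sample size of 68 patients per group was calculated", at two-sided 5% and 80% power. The same paragraph describes a trial of 140 women, and the Study design and Study population sections also give 140.

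**The concern.** A dropout allowance should separate two numbers: the women who must be evaluable for the stated power, and the larger number randomised so that this many remain. Here the first sentence gives 70 per group for 80% power, the dropout sentence gives 140 in total, and the two are the same number. So either 70 is the evaluable requirement and dropout was not added, or 70 already includes dropout and the sentence tying it to 80% power names the wrong quantity. The abstract's 68 per group makes 136, not 140, and is also said to include dropout.

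What is at stake is the power statement for the primary outcome. A reader cannot tell how many evaluable women the 80% refers to, and so cannot judge whether the attrition that occurs has used up the margin.

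**Working it through.** **Inputs.** Control rate p1 = 0.32 and patch rate p2 = 0.10 (Statistical analysis); difference d = 0.22. Alpha is 0.05, with two-sidedness stated only in the abstract. Power is 80% and dropout 10% (both places). Allocation is 1:1, implied by 70 per group and 140 in total. z(0.975) = 1.960 and z(0.80) = 0.842. The mean rate is 0.21.

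**Step 1. Evaluable women per group for 80% power, uncorrected.**
n = [1.960·√(2·0.21·0.79) + 0.842·√(0.32·0.68 + 0.10·0.90)]² / 0.22²
= [1.960·0.5760 + 0.842·0.5546]² / 0.0484 = (1.129 + 0.467)² / 0.0484 = 52.6, so **53**.

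**Step 2. The same with continuity correction.**
n′ = (n/4)·[1 + √(1 + 4/(n·d))]² = (52.6/4)·[1 + √(1 + 4/11.57)]² = 13.15·(2.160)² = 61.4, so **62**.

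**Step 3. Reproducing the plan's own figures.** Inflating for 10% dropout means dividing by 0.9.

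| Basis | Evaluable per group | After 10% dropout | Total |
|---|---|---|---|
| Uncorrected | 53 | 59 | 118 |
| Continuity-corrected | 62 (61.4 unrounded) | 69 (68.2 unrounded) | 138 (136 from 68) |

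The corrected route reproduces 68 to 70 per group and, rounded up, 140 in total. If the source rates were used as fractions 9/28 and 3/30 (an assumption, since the section gives only percentages), the corrected number is 61, and 61/0.9 = 67.8 gives exactly 68. So 68 and 70 both behave as numbers that already include dropout.

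**Step 4. Power at the two readings of 70.**
Uncorrected formula: z = (d·√n − 1.129)/0.5546.
- n = 70: (1.841 − 1.129)/0.5546 = 1.283, power 90.0%.
- n = 63 (70 × 0.9): (1.746 − 1.129)/0.5546 = 1.113, power 86.7%.

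Corrected formula: replace n by n·(1 − 1/(n·d))².
- n = 70: effective n = 61.2, power 85.7%.
- n = 63: effective n = 54.2, power 81.2%.

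Exact power comes from enumerating the two binomial distributions.

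| Evaluable per group | Normal, uncorrected | Normal, corrected | Exact, Pearson chi-square | Exact, Yates | Exact, Fisher |
|---|---|---|---|---|---|
| 70 | 90.0% | 85.7% | 91.2% | 86.7% | 87.4% |
| 63 | 86.7% | 81.2% | 87.6% | 82.9% | 82.9% |

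At 70 evaluable per group, no method gives 80%. At 63 evaluable, the corrected formula comes close to it.

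**The case against.** The strongest defence is that the number enrolled is right. Every section that states a total gives 140, and the stated rates, alpha, power and dropout lead to it through the continuity-corrected formula. On that view 68 is the calculated number, 140 is the planned total after rounding up, and the 80% simply describes the calculation from which 70 came. The part about enrolment stands. What it does not rescue is the wording: the section presents 70 as the number that gives 80% power, never states an evaluable number, and leaves the gap of two per group unexplained.

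Three stronger readings are tempting, and the document does not support them.

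- **A shortfall of 16 women.** A reader might infer that 70 per group are needed, so that 70/0.9 = 77.8, or 78 per group (156), should be randomised. But 32% versus 10% does not require 70 evaluable women; it requires 53 or 62.
- **The 80% is wrong however 70 is read.** It is wrong if 70 are analysed. If 70 are randomised and 63 analysed, the corrected formula gives 81.2%, consistent with a stated 80% after rounding up.
- **Dropout is uncovered because the target is a 66% relative reduction.** From 32% that means 10.9%. The corrected formula then gives 68 before dropout and 76 after it (152 in total), and 63 evaluable give about 77% by the corrected formula, 78.5% exact Yates or 83.9% exact Pearson. However, the Statistical analysis section names 32% versus 10% as its basis, and the abstract lists dropout among the assumptions behind 68. Calling the effect a 66% absolute difference, when the stated rates differ by 22 points, is a separate error and does not establish this reading.

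**Conclusion.** The link between sample size and power is wrong as worded. On the stated rates, 70 evaluable women per group give about 86–91% power rather than 80%, and 80% needs 53 (uncorrected) or 62 (corrected). The figures 68 and 70 are left unreconciled.

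The enrolment of 140 is adequate on those rates. With 10% dropout, about 63 per group remain, with 81–83% power corrected and 87–88% uncorrected. This is a reporting error in a figure on which the trial relies; it does not show that the trial is underpowered.

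The conclusion assumes rates of 32% and 10%, two-sided 5%, equal allocation and 10% dropout in each group. A one-sided test would move 70 further from 80% power (94.6% uncorrected at 70). That a continuity-corrected formula was used is inferred from the fit of the numbers; the document does not say so.

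**What to change.** State one calculation, in the same terms, in the abstract and in the Statistical analysis section. It should name the test or formula, the evaluable number per group required for 80% power, and the number randomised after the dropout allowance. Label 70 per group (140) as including dropout, with about 63 per group expected to be evaluable, and give the power for that number.

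The sponsor has to confirm which calculation was made:

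- If continuity-corrected: 62 evaluable per group, 68 to 69 after 10% dropout, rounded up to 70; power at 63 evaluable about 81% by the planning formula (83% exact).
- If the uncorrected chi-square was meant: 53 evaluable per group, 59 after dropout; 140 randomised then gives about 87% power at 63 evaluable.

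Either explain 68 as the calculated number that was rounded up to 70, or remove it. The cost is a few sentences. Enrolment, conduct and analysis do not change.

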## Methods/Design

### Aim of the study

Primary outcome variable:

2.1.1. To evaluate the incidence of symptomatic pelvic lymphoceles defined by CTCAE 4.03 grade ≥2 within 4 weeks after surgery in women undergoing open or laparoscopic pelvic lymphadenectomy for cervical and endometrial cancer with and without the application of Tachosil® during surgery.

Secondary outcome variables:

2.1.2 To evaluate the incidence of sonographically detected pelvic lymphoceles of at least 2 cm in the largest diameter 4 weeks after surgery in women undergoing open or laparoscopic pelvic lymphadenectomy for cervical and endometrial cancer with and without the application of Tachosil® during surgery.

2.1.3. To evaluate the rate and type of medical interventions for clinically symptomatic pelvic lymphoceles such as analgesics and/or lymphocele puncture and drainage.

2.1.4. To evaluate the rate of total and symptomatic lymphoceles between the three centers.

2.1.5. To evaluate the rate of total and symptomatic lymphoceles between cervical and endometrial cancer patients.

2.1.6. To evaluate the rate of total and symptomatic lymphoceles between the surgical device used for pelvic lymphadenectomy.

2.1.7. To evaluate the rate of total and symptomatic lymphoceles between patients with and without lymph node metastases.

2.1.8. To evaluate the risk for total and symptomatic lymphoceles depending on the total number of pelvic lymph nodes removed.

2.1.9. To evaluate the rate of total and symptomatic lymphoceles between patients with open and laparoscopic pelvic lymphadenectomy.

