## Discussion

The present randomized, controlled trial aims to evaluate the efficacy of Tachosil® in the prevention of symptomatic lymphoceles after pelvic lymphadenectomy in gynaecological malignancies. This is a clinical relevant topic as along with lymphedema, symptomatic lymphoceles are the major complication after pelvic lymphadenectomy. Recently, a study in patients with endometrial cancer described a prevalence of 23% for lymphedema after pelvic lymphadenectomy [10]. Due to the importance of this topic a prospective trial led by the Gynecologic Oncology Group has been released (GOG 244, GOG LEG study, The Lymphedema and Gynecologic Cancer Study).

In contrast to lymphedema, which is rather a chronic problem after pelvic lymphadenectomy, lymphoceles are more of an acute complication. The prevalence of lymphoceles after pelvic lymphadenectomy provided in the literature varies quite substantially between 11-63% [4, 5]. Symptomatic lymphoceles seem to occur in about 32% of patients undergoing pelvic lymphadenectomy [5]. This variation might be caused by numerous factors: the time interval between surgery and follow-up visit for lymphoceles as most of the small lymphoceles will spontaneously regress over time, rather small study populations in the majority of trials, the extent of lymphadenectomy, the use of new energy sources [5, 11]. Another interesting factor possibly influencing the rate of lymphoceles after pelvic lymphadenectomy might be the surgical approach. One study revealed a postoperative lymphocele rate of 15.4% and 1.4% in women after laparoscopic and after open pelvic lymphadenectomy, respectively [12]. Of note, this study retrospectively compared 138 women, who underwent systematic laparoscopic pelvic lymphadenectomy, to 123 historical control subjects, who underwent systematic pelvic lymphadenectomy via an open approach. Due to the design, this study has to be interpreted with caution [12]. In the present study, we aim to prospectively describe the lymphocele rates following open compared to laparoscopic systematic pelvic lymphadenectomy in women with gynecological malignancy.

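### Stratifying the primary test by surgical approach would be a free, modest gain over the crude chi-square; the crude test is not an error

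*Protocol article*

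**What the plan says.** The Statistical analysis section of the protocol article gives one method for proportions: "The chi-square test will used for comparisons of frequencies and cross-tabulations". It names no stratification or adjustment. The primary outcome (2.8.1) is a proportion, so as written the arms are compared crudely. The Study design section describes a computerized list and names no stratification factor.

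The sample size rests on a published trial "observing a rate of 32% of symptomatic lymphoceles in the placebo group and 10% in the Tachosil® group", and "Assuming a 10% drop out-rate, 140 women will be randomized".

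On surgical approach the article says three things:

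- Objective 2.1.9 compares lymphocele rates between open and laparoscopic surgery, so approach will be recorded.
- The Discussion treats approach as a possible influence: "One study revealed a postoperative lymphocele rate of 15.4% and 1.4% in women after laparoscopic and after open pelvic lymphadenectomy, respectively". It adds that this study was retrospective with historical open controls and calls for caution.
- The Background says that, on the available literature, complications do not clearly differ between the two routes.

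On centre, objective 2.1.4 reads "To evaluate the rate of total and symptomatic lymphoceles between the three centers". No section predicts a difference.

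**The concern.** Approach suits stratification well. The Treatment section has the envelope opened only after lymphadenectomy and hemostasis are finished, so the route of surgery, including any conversion up to that point, is fixed before anyone knows the arm and cannot be affected by it.

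If approach predicts symptomatic lymphocele, a crude test pays for ignoring it in two ways. Between-approach variation stays in the error term and lowers power. Chance imbalance in approach also stays in the estimated difference. Only about 26 primary events are expected (63 × 0.32 + 63 × 0.10 = 26.5), so such an imbalance could be visible in the result and lead to a disputed adjustment after the fact. Naming the stratified test in advance avoids both.

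**Working it through.** **Inputs from the article.** Two-sided alpha 0.05, 80% target power, 32% versus 10%, 10% dropout, 140 randomized. Evaluable women: 140 × 0.9 = 126, or 63 per arm.

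**Assumptions not in the article.** Laparoscopic share 50%, 70% or 85%; control-risk ratio by approach 1, 2, 4 or 11 (15.4 / 1.4 = 11); a constant treatment risk ratio of 0.10 / 0.32 = 0.3125; overall control risk held at 32%.

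**1. The plan's own figure.** Two-proportion formula, pooled risk 0.21:

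n = [1.96 × √(2 × 0.21 × 0.79) + 0.8416 × √(0.32 × 0.68 + 0.10 × 0.90)]² / 0.22² = 52.6, so 53 per group.

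With continuity correction this becomes 62, and 62 / 0.9 = 68.9, so 69 per group. That lies between the 68 of the abstract and the 70 of the Statistical analysis section. The planned size therefore reproduces with the continuity correction.

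**2. Crude power at 63 per arm, uncorrected test.**

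z = [0.22 − 1.96 × √(2 × 0.1659 / 63)] / √(0.3076 / 63) = 1.11, power 86.7%. Simulation gives 87.5%.

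**3. Stratified power.** At a 50:50 split the open-surgery control risk is 0.64 / (1 + ratio). In step 2, the pooled variance term 0.1659 and the alternative variance term 0.3076 are replaced by their within-stratum averages. Simulation uses the actual CMH statistic with unstratified allocation.

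| Ratio | Control risk, lap / open | Variance terms | Power by formula | Crude, simulated | CMH, simulated |
|---|---|---|---|---|---|
| 1:1 | 32% / 32% | 0.1659; 0.3076 | 86.7% | 87.5% | 87.5% |
| 2:1 | 42.7% / 21.3% | 0.1610; 0.2951 | 87.8% | 87.5% | 88.6% |
| 4:1 | 51.2% / 12.8% | 0.1500; 0.2671 | 90.3% | 87.5% | 90.7% |
| 11:1 | 58.7% / 5.3% | 0.1353; 0.2295 | 93.5% | 87.6% | 93.3% |

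**4. Other laparoscopic shares (simulated CMH; crude about 87.5% throughout).** At 70%: 88.3% (2:1), 89.4% (4:1), 90.5% (11:1). At 85%: 87.9%, 88.5%, 89.0%. The gains are therefore about 0.5 to 3 points. At 30% laparoscopic the 11:1 gain would reach about 10 points, but only with an 88% control rate after laparoscopy, which is not credible.

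**5. Type I error.** Stratified by approach, 4.8% to 5.0% across these scenarios. The crude test also holds 5% under unstratified allocation.

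**6. Chance imbalance at 50:50.** The laparoscopic share within an arm has SD √(0.25 / 63) = 0.063. At 11:1 the risk gap between approaches is 0.533 in controls and 0.533 × 0.3125 = 0.167 in treated women. At the planned effect the crude difference therefore moves with SD 0.063 × √(0.533² + 0.167²) = 0.035, a 95% range of about ±7 points. The same formula gives about ±5 points at 4:1 and ±3 at 2:1.

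**7. Adding centre (six strata, about 126 / 6 = 21 women each).** If neither factor is prognostic, power is 86.4% against 87.4% crude, a loss of 1 point. At 2:1 by approach with no centre effect, nothing is gained (87.6% against 87.7%). With an assumed centre effect alone (risk multipliers 0.6, 1 and 1.4), nothing is gained either.

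**The case against.** The strongest reply is that nothing here is wrong. Under an unstratified list the crude chi-square is valid, power at 126 evaluable women already exceeds the 80% target, and a condensed article may leave covariate adjustment to an analysis plan that is not shown. Validity and adequate power on the planned rates are conceded. What remains is that the article does name a test, and a better one is available from data it will collect.

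Three stronger readings are tempting, and the article does not support them.

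- **That approach is known to change the risk tenfold.** The 11:1 figure comes from one study that the article itself discounts, it concerns lymphoceles in general and not the symptomatic endpoint, and the Background points the other way. At the planned 32% and a 50:50 split it needs a 58.7% symptomatic rate in laparoscopic controls. The all-laparoscopic historical control cohort in the Discussion had 17.2% symptomatic and 51.7% total lymphoceles. If 15.4% and 1.4% are instead taken literally as control rates, overall control risk at 50:50 is 8.4%, crude power is about 28%, and stratifying adds only about 1 point.
- **That centre differences are expected and centre must be in the primary test.** Objective 2.1.4 only plans a comparison, and step 7 shows little reward for the extra strata.
- **That the crude test has the wrong type I error, or that imbalance could move the estimate by 9 points.** The first requires a list stratified by approach, which is nowhere described; envelopes follow inclusion number. The second (1.96 × √(2 × 0.25 / 63) × 0.533 = 0.093) holds only with no treatment effect at 11:1; at the planned effect it is about 7.

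**Conclusion.** This holds as an optional gain in efficiency, not as a defect. Stratifying the primary test by approach keeps type I error at about 5% and costs no power if approach does not matter. At a 50:50 split it adds about 1 point at a 2:1 risk ratio, about 3 at 4:1 and 5 to 6 at 11:1; with 70 to 85% laparoscopic, about 0.5 to 3. The 2:1 and 4:1 rows are the more realistic guide.

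The figures rest on the planned 32% and 10%, 63 evaluable per arm, a constant treatment risk ratio, and assumed approach shares and risk ratios that the article does not give. The direction does not depend on the exact values: across the ratios and shares examined at the planned rates, CMH by approach was never materially worse than the crude test.

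**What to change.** In the Statistical analysis section, state that the primary outcome will be compared by a Cochran-Mantel-Haenszel test stratified by surgical approach (open or laparoscopic, as it stands when allocation is revealed), reported with the Mantel-Haenszel risk difference and its 95% confidence interval, and that the crude chi-square will be a sensitivity analysis.

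The cost is one sentence, with no extra patients or data. It should be fixed before outcome data are compared by arm. Centre may be added as a second stratification factor if the investigators have reason to expect it to matter; the price is about 1 point of power if neither factor is prognostic.

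### The secondary outcomes are listed in three inconsistent ways, so the Bonferroni level for a secondary result depends on which list is followed

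*Protocol article*

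**What the plan says.** All references are to the protocol article.

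- **Statistical analysis** sets the multiplicity rule: "Bonferroni’s correction will be used for multiple comparisons of secondary outcomes". It gives neither the number of comparisons nor the family.
- **Abstract, Methods/Design** gives one list: "Secondary outcomes are asymptomatic lymphocele verified by ultrasound, medical or surgical intervention".
- **Aim of the study** puts eight items, 2.1.2 to 2.1.9, under its secondary heading. Item 2.1.2 is sonographic lymphocele of at least 2 cm and 2.1.3 is medical intervention. The other six compare lymphocele rates by centre, tumour type, surgical device, nodal status, number of nodes removed and surgical approach. Item 2.1.4, for example, is "To evaluate the rate of total and symptomatic lymphoceles between the three centers". Each of the six is worded for both total and symptomatic lymphoceles.
- **Outcome variables** tags four items as secondary, 2.8.2 to 2.8.5. Item 2.8.2 is "The incidence of sonographically detected pelvic lymphoceles of at least 2 cm in the largest diameter 4 weeks after surgery" and 2.8.3 is medical intervention. Length of hospital stay (2.8.4) and predefined complications (2.8.5) appear in neither of the other lists, and the six factor comparisons are absent.

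**The concern.** A Bonferroni level is the overall level divided by the number of tests, so it is fixed only when the list of tests is fixed. Here the article supports more than one list, and nothing says which governs. The same p-value could be declared significant or not according to a choice still open when the data are seen.

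Two features make this more than untidy drafting. First, the six comparisons 2.1.4 to 2.1.9 carry the secondary label but do not compare randomised arms. If they count towards the divisor, they tighten the level for the questions that randomisation can answer.

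Second, the sonographic outcome has two meanings. Items 2.1.2 and 2.8.2 count any lymphocele of at least 2 cm, with or without symptoms. The abstract counts asymptomatic ones only. Under the abstract's wording, a lymphocele that the patch turned from symptomatic to asymptomatic would become an added event in the treated arm, while a symptomatic lymphocele in a control woman would not count. The two versions therefore answer different questions.

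**Working it through.** **1. The lists side by side**

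| Item | Abstract | Aim of the study | Outcome variables |
|---|---|---|---|
| Sonographic lymphocele | asymptomatic only | any, at least 2 cm (2.1.2) | any, at least 2 cm (2.8.2) |
| Intervention | yes | 2.1.3 | 2.8.3 |
| Six factor comparisons | no | 2.1.4 to 2.1.9 | no |
| Hospital stay | no | no | 2.8.4 |
| Predefined complications | no | no | 2.8.5 |

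Only the sonographic and intervention items recur in all three, and the sonographic item is not defined alike.

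**2. Level per test**, 0.05/m:

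- Outcome variables, m = 4: 0.05/4 = 0.0125.
- Aim of the study, one test per item, m = 8: 0.05/8 = 0.00625.
- Aim of the study, total and symptomatic tested separately, m = 2 + 6 × 2 = 14: 0.05/14 = 0.0036.

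A result with p = 0.008 passes the first level and fails the other two.

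**3. The plan's own sample size.** Inputs are "Assuming a two-sided 5% significance level, a power of 80%, and a drop out rate of 10" per cent (abstract), and "a rate of 32% of symptomatic lymphoceles in the placebo group and 10% in the Tachosil® group" (Statistical analysis). The two-proportion formula with continuity correction gives 62 per group. Allowing for dropout, 62/0.9 = 68.9, so 69, close to both the abstract's 68 and the 70 in Statistical analysis. The trial is therefore sized for the primary test at 0.05, with no allowance for adjusted secondary tests. Evaluable women per arm: 70 × 0.9 = 63.

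**4. Effect on power for one binary secondary outcome.** Normal approximation: power = Φ[(d − z × SE0)/SE1], where d is the difference in rates and z is the two-sided critical value at 0.05/m. The rates 32% and 12% are assumed for illustration.

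- d = 0.20 and mean rate 0.22
- SE0 = √(0.22 × 0.78 × 2/63) = 0.0738
- SE1 = √[(0.32 × 0.68 + 0.12 × 0.88)/63] = 0.0716

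| m | Level | z | Power |
|---|---|---|---|
| 1 | 0.05 | 1.960 | 0.78 |
| 4 | 0.0125 | 2.498 | 0.59 |
| 8 | 0.00625 | 2.734 | 0.49 |
| 14 | 0.0036 | 2.914 | 0.42 |

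**5. Range over other rates**, same formula and 63 per arm:

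| Rates | m = 1 | m = 4 | m = 8 | m = 14 |
|---|---|---|---|---|
| 32% vs 10% (the primary planning rates, borrowed) | 0.87 | 0.71 | 0.62 | 0.55 |
| 57.7% vs 23.3% (percentages printed for the cited randomised trial in women) | 0.98 | 0.94 | 0.90 | 0.86 |

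The loss is substantial for a moderate effect and modest for a very large one.

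**The case against.** **The analysis plan may settle it.** Family membership and the divisor are commonly left to the SAP, which is not shown. That is fair as far as the missing number goes. It does not reach the contradiction: no SAP can agree with three lists that differ in content and in the definition of the sonographic outcome.

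**The multiplicity sentence can be read narrowly.** It could cover only the four items tagged as secondary in Outcome variables, or pairwise comparisons among the three centres. This stands. A reader might infer that every listed item goes into one correction and that power is therefore wasted. The article neither says that all lists form one family nor exempts the factor comparisons, so what can be asserted is only that the level depends on the reading. The count of 14 is also one choice among several.

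**The sonographic conflict is one word in an abstract.** Items 2.1.2 and 2.8.2 agree closely with each other, which is a good reason to let them govern. The abstract still states a different outcome and should be aligned.

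**A stronger reading of the sonographic conflict is not supported.** A reader might infer that counting only asymptomatic lymphoceles would conceal most of the patch's effect, by treating 57.7% and 23.3% as total rates and subtracting the symptomatic rates. Background and Discussion both label those figures asymptomatic, and the control count printed with them, 9/28, is 32.1% rather than 57.7%. No size can be put on this from such figures.

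**Bonferroni is valid.** It is, and naming it is not an error. Holm is proposed as an improvement: it controls the same familywise error and is never less powerful.

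**Conclusion.** The point holds as an internal inconsistency with a practical consequence. The article gives three secondary lists and two meanings of the sonographic outcome, and labels six comparisons outside the randomised arms as secondary. The per-test level is consequently 0.0125, 0.00625 or 0.0036 according to the list and the counting. In the illustration of 32% against 12% with 63 evaluable women per arm, power runs from about 59% at four tests to 42% at fourteen. Those rates are assumed, and the loss is smaller for larger effects. The primary comparison at 0.05 is not touched. This should be corrected, but it does not threaten the main conclusion of the trial.

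**What to change.** 1. Use one list of secondary outcomes in the abstract, Aim of the study and Outcome variables.
2. Keep the definition in 2.1.2 and 2.8.2, stating that any sonographic lymphocele of at least 2 cm counts regardless of symptoms, and align the abstract to it.
3. Limit the multiplicity family to the comparisons between randomised arms, 2.8.2 to 2.8.5, state its size, and use Holm's procedure in place of Bonferroni.
4. Report 2.1.4 to 2.1.9 as exploratory estimates with confidence intervals, outside the family.

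The cost is wording only, with no added patients, visits or measurements. The small downside is that no formal significance claim can be made for the comparisons by centre, tumour type, device, nodal status, node count or approach. The article never expressly gives them confirmatory standing, so little is given up.
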